| **Drug Administration Plan** | The dosing phase of this study includes three stages: the single-dose phase, the multiple-dose phase, and the extended dosing phase. The pharmacokinetics of the single-dose and multiple-dose administrations are combined, during which safety, tolerability, and preliminary efficacy are observed.  **1. Single-Dose Phase**  The single-dose escalation phase will begin with the starting dose and proceed in an ascending order from low to high doses, with 3 to 6 subjects enrolled in each dose group. In each dose group, 3 subjects will be enrolled sequentially, and a single dose will be administered on Day 1 (D1) at that dose, followed by a 6-day observation period (D2-D7). Each subject will receive treatment with a single dose.  **2. Multiple-Dose Phase**  After completing the pharmacokinetic blood sampling for the single-dose administration, if the subject is well-tolerated, they will enter the multiple-dose phase, with doses administered on Days 8, 11, and 15. Each subject will receive the same dose as in the single-dose phase, with the dose-limiting toxicity (DLT) observation period defined as the first administration to 25 days after the first dose. Initially, only one subject will be enrolled in each dose group to observe their tolerability and safety within the 25 days following the first dose. Only if this subject does not experience a DLT will the remaining two subjects in the same dose group be allowed to enroll simultaneously.  If none of the 3 subjects in a dose group experience DLT, the trial will proceed to the next dose group. If 1 out of the 3 subjects in a dose group experiences DLT, an additional 3 subjects will be recruited to receive the same dose of the investigational drug, and they will be monitored for DLT occurrence.  If 1 DLT occurs among the 6 subjects, the trial will proceed to the next dose group. If 2 or more DLTs occur among the 3 subjects, or if 2 or more DLTs occur among the 6 subjects, the trial will be reduced to the previous dose group. If the previous dose group has fewer than 6 evaluable subjects, an additional 3 subjects will be enrolled to bring the total number of evaluable subjects to 6. If no more than 1 DLT occurs among the 6 evaluable subjects, the trial will be halted, and that dose group will be declared as the maximum tolerated dose (MTD). If the previous dose group has already reached 6 evaluable subjects, the trial will be halted, and that dose will be declared as the MTD.  During the multiple-dose escalation trial, real-time analysis of the pharmacokinetic (PK) data for the selected dose groups will be conducted to determine whether the drug reaches a saturation state in the body based on PK and pharmacodynamic (PD) indicators.  **3. Extended Treatment Phase**  After completing the single-dose and multiple-dose phases, if the efficacy assessment indicates clinical benefit for the subject, they will enter the extended dosing phase. In the extended dosing phase, treatment may continue according to the original dosing regimen or with adjustments to the dose based on the subject's tolerability and existing clinical results. Each dosing cycle lasts 21 days, with doses administered on Days 1, 4, 8, and 11 of each cycle. The number of extended dosing cycles will vary based on the patient's efficacy; subjects who achieve an objective response rate of partial response (PR) or higher after 6 cycles may continue receiving the treatment until disease progression, while those who do not reach PR will discontinue the treatment. Efficacy and safety data will continue to be collected during the extended dosing phase. |

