**2）Dose Reduction and Treatment Interruption**

If a subject experiences a dose-limiting toxicity (DLT) during the single-dose or multiple-dose phases, treatment must be interrupted until the toxicity recovers to Grade 1 or below. Based on the investigator's judgment that the subject may benefit from continued treatment, the subject may resume medication.

In the continuation dosing phase, the dose may be adjusted or treatment may be interrupted according to the following rules:

| **Toxicity** | **CTCAE Grade** | **Measures** |
| --- | --- | --- |
| Nausea and vomiting | Grade 3-4 | If it occurs for the first time, consider using antiemetics for treatment and interrupt the medication until the toxicity recovers to Grade 1 or below. Continue treatment with the original dose, and it is recommended to use antiemetics as a preventive measure.  If it occurs again, interrupt the medication until recovery to Grade 1 or below, and reduce the dose to the previous level. |
| Diarrhea | Grade 3 | If it occurs for the first time, consider using antidiarrheal medication for treatment and interrupt the medication until the toxicity recovers to Grade 1 or below. Continue treatment with the original dose, and it is recommended to use antidiarrheal medication as a preventive measure.  If it occurs again, interrupt the medication until recovery to Grade 1 or below, and when resuming treatment, reduce the dose to the previous level. |
|  | Grade 4 | If it occurs for the first time, consider using antidiarrheal medication for treatment and interrupt the medication until the toxicity recovers to Grade 1 or below. Adjust the dose to the previous level for treatment, and it is recommended to use antidiarrheal medication as a preventive measure.  If it occurs again, discontinue treatment and withdraw from the study. |
| Neutropenia | Grade 3 | ANC: 0.75 - 1.0 × 10^9^ /L, maintain the current dose and continue treatment. ANC: 0.5 - 0.75 × 10^9^ /L, interrupt treatment until ANC recovers to 1.0 × 10^9^ /L, then continue treatment at the original dose. |
| Febrile neutropenia | Grade 3 | Interrupt treatment until ANC recovers to 1.0 × 10^9 /L; when resuming treatment, reduce the dose to the previous level. |
| Thrombocytopenia | Grade 3 | Maintain the current dose of treatment and monitor platelet counts weekly |

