|  | Grade 3-4 | Grade 3 thrombocytopenia with bleeding: interrupt treatment until PLT recovers to 50 × 10^9^ /L; when resuming treatment, reduce the dose to the previous level and monitor platelet counts weekly.  Grade 4 thrombocytopenia: interrupt treatment until PLT recovers to 50 × 10^9^ /L; when resuming treatment, reduce the dose to the previous level and monitor platelet counts weekly. |
| Anemia | Grade 3 | Interrupt treatment until Hb recovers to 10 g/dL; when resuming treatment, reduce the dose to the previous level. |
| QTc interval prolongation | Grade 2 | If it occurs for the first time: interrupt treatment until QTc < 450 ms; when resuming treatment, reduce the dose to the previous level.  If it occurs again: discontinue treatment and withdraw from the study. |
| Neurotoxicity | Grade 2 | If it occurs for the first time: interrupt treatment until the toxicity recovers to Grade 1 or below; when resuming treatment, reduce the dose to the previous level.  If it occurs again: discontinue treatment and withdraw from the study. |
| Liver function (elevated ALT and AST levels) | Grade 2 | Baseline normal, with Grade 2 elevation of ALT or AST occurring after treatment.  If it occurs for the first time: interrupt medication until toxicity recovers to Grade 1 or below; when resuming medication, reduce the dose by one level and increase the frequency of liver function monitoring.  If it occurs again: discontinue treatment and withdraw from the study. |
|  | Grade 3 | For patients with normal baseline, if Grade 3 toxicity occurs with ALT or AST > 8 × ULN, discontinue treatment and withdraw from the study.  For patients with Grade 1 baseline, if Grade 3 toxicity occurs with ALT or AST > 8 × ULN, consider discontinuing treatment and withdrawing from the study.  For patients with normal baseline or Grade 1 baseline, if Grade 3 toxicity occurs for the first time with 5 × ULN < ALT or AST < 8 × ULN, interrupt medication until toxicity recovers to Grade 1 or below; when resuming medication, reduce the dose by one level and increase the frequency of liver function monitoring. If it occurs again, discontinue treatment and withdraw from the study. |
|  | Grade 4 | Discontinue treatment and withdraw from the study. |
| Others | Grade 2-3 | For relapsedGrade 2-3 toxicities, except for alopecia and fatigue, treatment must be interrupted until the toxicity recovers to Grade 1 or below; when resuming treatment, reduce the dose to the previous level. |

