## Definition of DLT

Any drug-related toxicity occurring within 25 days after the first dose of the investigational drug, as defined by CTCAE version 5.0, that is considered related to the investigational drug (including definitely related, probably related, or possibly related) will be regarded as a DLT:

1. Hematologic Toxicity

- Grade 3 febrile neutropenia, defined as an absolute neutrophil count (ANC) < 1.0 × 10^9^/L accompanied by fever, with a temperature > 38.3℃, or a temperature sustained ≥ 38.0℃ for more than 1 hour;
- Grade 4 neutropenia without fever lasting ≥ 5 days;
- Grade 3 thrombocytopenia (25×10^9^/L < platelet count≤50×10^9^/L) accompanied by bleeding of Grade 2 or higher according to the WHO bleeding classification (2017 revised version), or Grade 4 thrombocytopenia lasting≥7 days with platelet transfusion treatment occurring≥2 times (excluding acute leukemia patients).

1. Any Grade 3 or higher non-hematologic toxicity, including but not limited to:

- Grade 3 or higher QT interval prolongation;
- Hepatic toxicity: If the baseline levels of ALT, AST, or TBIL for the subject are ≤ Grade 1, then drug-related Grade 3 toxicity will be considered as DLT.

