## Multiple-Dose Administration Phase（D8-D25）

After the single-dose administration phase is completed, if the subject tolerates the treatment well, they will enter the multiple-dose administration phase.

- IV Infusion Administration on D8, D11, and D15
- PK Blood Sample Collection:

On D11: collect blood samples 0.5 hours before administration.

On D15: collect blood samples within 0.5 hours before administration, and at 5 minutes, 10 minutes, 20 minutes, 30 minutes (immediately after administration), 32 minutes, 35 minutes, 45 minutes, 1 hour, 2 hours, 4 hours, 8 hours, and 12 hours after administration (3 mL each time).

- Biomarker Blood Sample Collection (only for leukemia patients):

On D8: collect blood samples within 0.5 hours before administration, and at 1 hour, 4 hours, and 24 hours (D9) after administration (4 mL each time).

On D11: collect blood samples within 0.5 hours before administration and at 1 hour after administration (4 mL each time).

On D15: collect blood samples within 0.5 hours before administration, and at 1 hour, 4 hours, 24 hours (D16), 48 hours (D17), and 72 hours (D18) after administration (4 mL each time).

- Vital Signs: Including temperature, heart rate, respiratory rate, and blood pressure (systolic and diastolic), to be checked once within 0.5 hours before each administration and again 2 hours after administration on D8, D11, and D15, as well as once on D25.
- Physical Examination: Includes examination of the skin, mucous membranes, lymph nodes, head, neck, chest, abdomen, spine/extremities, and nervous system. This will be conducted once on D11, D15, and D25.
- Laboratory Tests: These will be conducted once on D11, D15, and D25.
- Complete Blood Count (CBC): Red blood cell count, hemoglobin, platelet count, white blood cell count, neutrophil count, lymphocyte count.
- Urinalysis: Urine protein, urine red blood cells, urine white blood cells.
- Blood Biochemistry: Blood creatinine, urea, total bilirubin, alanine transaminase (ALT), aspartate transaminase (AST), alkaline phosphatase, total protein, albumin, electrolytes (K+, Na+, Ca2+, Mg2+, Cl-), total cholesterol, low-density lipoprotein (LDL), high-density lipoprotein (HDL), creatine kinase (CK), creatine kinase isoenzyme (CK-MB), α-hydroxybutyrate dehydrogenase (α-HBDH), lactate dehydrogenase (LDH), fasting blood glucose.
- Coagulation Function: Prothrombin time (PT), activated partial thromboplastin time (APTT), thrombin time (TT), fibrinogen (FIB).

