**Liver Toxicity**

In the event of liver toxicity, additional clinical information should be collected to determine the most likely cause of the observed liver abnormalities. This includes identifying abnormalities in liver function indicators that may be due to other factors, such as concomitant medications, alcoholic and autoimmune hepatitis, tumor metastasis, disease progression, viral hepatitis, cardiovascular disease, and other causes. The following measures should be taken:

Grade 2 Toxicity

- Continue to closely monitor liver function indicators during the Purinostat Mesylate treatment cycle until they return to baseline levels.
- For patients with baseline normal liver function who experience a Grade 2 increase in ALT or AST after treatment, suspend treatment until liver function returns to Grade 1 or below. Upon resuming treatment, the dose should be reduced by one level, and the frequency of liver function monitoring should be increased.

Grade 3 Toxicity

- If ALT or AST> 5×ULN, treatment should be discontinued, and the subject should exit the study. The subject will receive a consultation from a liver disease specialist.
- Closely monitor liver function indicators. If liver function is severely impaired relative to baseline values or reaches the level of severe liver injury, the medication should be discontinued, and supportive care should be strengthened, such as bed rest and close monitoring of liver function indicators, until liver function returns to baseline levels.
- During the process of reducing the dose by one level, if Grade 2 or higher toxicity recurs, treatment should be discontinued, and the subject should exit the study.

Grade 4 Toxicity

- Treatment should be discontinued, and the subject should exit the study. The subject will receive a consultation from a liver disease specialist.

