**Cardiac Toxicity**

Grade 2 Toxicity

- Suspend treatment and increase the frequency of ECG monitoring until QTc<450 ms.
- Correct any electrolyte imbalances and discontinue any medications that may prolong the QTc interval.
- If toxicity can be restored to Grade 1 or below within 14 days, reduce the dose for treatment and continue to increase the frequency of ECG monitoring; otherwise, treatment should be discontinued, and the subject should exit the study.
- If Grade 2 toxicity recurs, treatment should be discontinued, and the subject should exit the study.

≥ Grade 3 Toxicity

- Treatment should be discontinued, and the subject should exit the study. The subject will receive a consultation from a cardiology specialist.

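### Sections 3.2.5 and 8.4 contradict each other on when raised ALT/AST ends treatment, and resumption after a DLT is not made subject to the exits in section 8.4

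*Protocol*

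**What the plan says.** Two parts of the protocol tell the investigator what to do after a toxicity.

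Section 3.2.5 (Individual Dose Adjustment, part 2) has two components:

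- **Single- and multiple-dose phases (D1-D25).** After a DLT, treatment stops until recovery to Grade 1 or below. If the investigator then judges that "the subject may benefit from continued treatment, the subject may resume medication". No type of toxicity is excepted and no resumption dose is given.
- **Continuation phase.** A table sets rules by toxicity. In the Grade 3 liver row, for a normal or Grade 1 baseline, "if Grade 3 toxicity occurs for the first time with 5 × ULN < ALT or AST < 8 × ULN, interrupt medication"; dosing then restarts one level lower with closer liver monitoring. Above 8×ULN, a subject with normal baseline leaves the study, while for one with Grade 1 baseline withdrawal is only to be considered.

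Section 8.4 (Risk Control Plan) names no phase:

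- **Liver, Grade 3:** "If ALT or AST> 5×ULN, treatment should be discontinued, and the subject should exit the study".
- **Cardiac, Grade 3 or higher:** "Treatment should be discontinued, and the subject should exit the study. The subject will receive a consultation from a cardiology specialist".

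Section 3.4 counts as DLTs both "Grade 3 or higher QT interval prolongation" and drug-related Grade 3 hepatic toxicity in subjects whose baseline is Grade 1 or below. Sections 3.2.5 and 8.4 do not refer to each other.

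**The concern.** In the continuation phase, a subject with a first ALT or AST rise of, say, 6×ULN is to be dosed again one level lower under section 3.2.5 and is to leave the study under section 8.4. Both rules are specific and numeric and address the same event, so whichever the investigator follows departs from the other.

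In D1-D25 the problem is softer. The DLT paragraph of section 3.2.5 permits resumption in general terms, and section 8.4 removes subjects with particular toxicities. An investigator who reads only the dose-adjustment section finds nothing against re-exposing a subject whose Grade 3 QT or ALT/AST DLT has recovered.

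At stake is the safety of subjects who might be dosed again, and whether two subjects with the same event are handled alike. These toxicities are foreseeable: section 8.3.1 lists QTc prolongation and ALT/AST elevation among the anticipated events.

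**Working it through.** No sample size, error rate or event count is at issue, so the check sets the rules side by side by toxicity, grade and phase.

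**Liver, continuation phase**

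| Event | Section 3.2.5 table | Section 8.4 | Result |
| --- | --- | --- | --- |
| Grade 2, normal baseline, first event | Interrupt, resume one level lower | Suspend, resume one level lower | Agree |
| Grade 3, 5-8×ULN, first event, normal or Grade 1 baseline | Interrupt, resume one level lower | Exit | Contradict |
| Grade 3, >8×ULN, normal baseline | Exit | Exit | Agree |
| Grade 3, >8×ULN, Grade 1 baseline | Consider withdrawal | Exit | Contradict |
| Grade 4 | Exit | Exit | Agree |

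The two sections match at Grade 2 and Grade 4 and diverge only within Grade 3. The cause is two cut-offs, 5×ULN in section 8.4 and 8×ULN in section 3.2.5, together with a weaker instruction for Grade 1 baseline.

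**Liver, D1-D25**

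1. Section 4.4 caps ALT, AST and total bilirubin at 1.5×ULN at entry.
2. Appendix 14.3 runs Grade 1 to 2.5×ULN for ALT and AST and to 1.5×ULN for bilirubin.
3. Since 1.5 < 2.5 for ALT and AST, and 1.5 = 1.5 for bilirubin, every subject enrolled within criteria has a baseline of Grade 1 or below.
4. A drug-related Grade 3 ALT or AST rise in D1-D25 is therefore a DLT under section 3.4 for all of them. Once it recovers, section 3.2.5 permits resumption; section 8.4 says exit above 5×ULN.

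**QT, D1-D25**

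1. QT prolongation of Grade 3 or higher is a DLT under section 3.4.
2. The exit rule in section 8.4 is headed cardiac toxicity. Its Grade 2 items are written in terms of QTc, so Grade 3 or higher QT prolongation falls under it.
3. Once the event recovers, section 3.2.5 permits resumption; section 8.4 says exit.
4. The strictness is also out of order. After a first Grade 2 QTc event in the continuation phase, the table says "interrupt treatment until QTc < 450 ms; when resuming treatment, reduce the dose to the previous level". After the more severe event in D1-D25, the DLT paragraph states neither a reduction nor an exit.

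**Does anything else settle it?**

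- Section 4.6 considers ending participation for intolerable toxicity only when there is no recovery within 14 days. The cases here are those that recover.
- Section 6.3 says that "if the subject tolerates the treatment well, they will enter the multiple-dose administration phase". This is an undefined judgment at entry to that phase, not a check before the D11 or D15 dose.

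**Effect on the primary objective.** Under section 3.2.4 a subject with a DLT after at least one dose is evaluable whatever happens next. The DLT is counted whether or not dosing resumes, so the 3+3 decisions and the MTD are the same under either rule.

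**The case against.** The best defence concerns D1-D25. The DLT paragraph obliges the investigator to interrupt and then only permits resumption. Section 8.4 sets specific stops for anticipated events. A general permission and a specific stop can both be obeyed, and following section 8.4 breaches nothing in the DLT paragraph. That stands: these two items are missing precedence wording, not outright contradictions. It does not help with the continuation-phase liver rules, where one specific instruction to resume meets one specific instruction to leave.

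Section 8.4 also says *should*, and its Grade 3 liver block is loosely drafted: it speaks of stopping until liver function is back at baseline and of recurrence while the dose is being lowered by one level. That may mean dose reduction was contemplated at Grade 3, or it may carry over from the Grade 2 rule. Either way the block needs clarifying.

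Several stronger readings are tempting but not supported:

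- **Re-exposure at the full dose is prescribed.** The synopsis says "Each subject will receive the same dose as in the single-dose phase", but this describes the planned schedule for subjects who tolerate treatment. The DLT paragraph is silent on the resumption dose, and section 8.1.4 lets the investigator adjust the dose for adverse events.
- **A rise of 5-8×ULN meets three rules.** The DLT paragraph covers D1-D25 and the table covers continuation, so any one event meets at most two.
- **The doses open to re-exposure can be counted from the D1, D8, D11 and D15 schedule.** The protocol does not say whether interrupted doses are lost or delayed, so no count follows.
- **The continuation table contradicts the cardiac exit.** Its QTc row covers Grade 2 only, and there it agrees with section 8.4 on interruption and dose reduction.

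**Conclusion.** The ALT/AST rules are contradictory as written. In the continuation phase there are two conflicts: a first rise of 5-8×ULN with normal or Grade 1 baseline, and a rise above 8×ULN with Grade 1 baseline. In D1-D25 there are two gaps, for ALT/AST above 5×ULN and for cardiac toxicity of Grade 3 or higher including QT, where discretionary resumption is not made subject to the exits in section 8.4.

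This rests on reading section 8.4 as applying to all phases, since it names none, and on reading its cardiac rule as covering QT. The consequence is limited to the safety and consistent handling of subjects who are dosed again. A reader might infer that dose finding is compromised; it is not, because DLT counts, escalation and the MTD do not depend on which rule is followed. The trial has a single center, so the concern is inconsistency between subjects rather than between sites. The point should be corrected, as a patient-safety matter that needs only wording.

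**What to change.** - **Section 3.2.5 table and section 8.4, liver:** use one ALT/AST exit threshold in both, for normal and Grade 1 baselines alike. Take the stricter value, above 5×ULN, unless the sponsor justifies 8×ULN. If 8×ULN is chosen, section 8.4 must carry the interruption and one-level reduction for 5-8×ULN.
- **Section 8.4, Grade 3 liver block:** state whether the dose-reduction wording refers to the Grade 2 rule or to Grade 3, and align it with the chosen threshold.
- **Section 3.2.5, DLT paragraph:** make resumption after a D1-D25 DLT subject to section 8.4, and state that there is no re-exposure after QT prolongation of Grade 3 or higher.

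The cost is a protocol amendment to wording in two sections. It needs no extra patients or procedures.

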## Concomitant Medication

### Permitted Concomitant Medications

From the date of signing the informed consent form, any concomitant treatments or changes in concomitant medications that subjects must receive during the trial must be recorded by the investigator in the corresponding section of the eCRF, including the drug name, dosage, administration times, and indications.

During the screening period and throughout the trial, subjects are allowed to use the following medications:

- Supportive treatment for tumors and adverse events occurring during the trial, such as antibiotics, antiemetics, antidiarrheals, antipyretics, antihistamines, analgesics, medications to increase white blood cell counts, and medications to control high white blood cell counts (e.g., hydroxyurea), etc.;
- Corticosteroids: prednisone < 20 mg/day or equivalent doses of other corticosteroids for the treatment of conditions unrelated to the disease under study; if using prednisone > 20 mg/day or equivalent doses of other corticosteroids, the duration should not exceed 4 days for the prevention or treatment of adverse events occurring during the trial (e.g., infusion reactions);
- Others: Baseline medications for concomitant conditions such as hypertension or diabetes that the investigator deems will not affect the observation of study endpoints and can be used concomitantly.

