## Definition of MTD

Within 25 days after the first dose, if ≤ 1 DLT occurs among 6 subjects, the highest dose that meets this criterion will be defined as the MTD. If all dose groups specified in the protocol have been completed and no DLT occurs in the highest dose group, then the highest dose will be determined as the MTD.

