## Inclusion Criteria

1. Age between 18 and 70 years, regardless of gender.
2. Diagnosis confirmed by histopathological or cytological examination (according to the "Diagnostic Criteria and Efficacy Standards for Hematological Diseases" (4th Edition) published by Science Press) for hematological malignancies, including but not limited to B-cell lymphoma, multiple myeloma, B-cell acute leukemia, T-cell lymphoma, and T-cell acute leukemia. Patients must have experienced disease progression, relapse, or be unsuitable for standard treatment after receiving standard treatment regimens (specific definitions for relapsed or refractory disease can be found in Section 4.2).
3. No severe organic lesions in the heart, lungs, liver, or kidneys (LVEF≥50%; total bilirubin ≤1.5×ULN; ALT ≤1.5×ULN; AST ≤1.5×ULN; serum creatinine ≤1.5×ULN or CCr > 40 mL/min).
4. No severe coagulation dysfunction (PT≤1.5×ULN, APTT≤1.5×ULN, TT≤1.5× ULN, and FIB≥1.0 g/L).
5. No severe hematological abnormalities (absolute neutrophil count≥1.5×10^9^/L, platelets≥75×10^9^/L, hemoglobin≥80 g/L), and no transfusion of platelets, red blood cells, or hemoglobin within the 2 weeks prior to screening.
6. At least 4 weeks or more than 5 half-lives since the last anti-tumor treatment (chemotherapy, radiotherapy, biological therapy, or immunotherapy) prior to enrollment.
7. Expected survival time of≥12 weeks.
8. ECOG performance status of≤2.
9. Willingness to participate in the study and sign the informed consent form.

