**Hematologic toxicity**

Hematological adverse reactions (thrombocytopenia, neutropenia, anemia) commonly occur during the early stages of treatment. Close monitoring of complete blood count (CBC) is essential, and adjustments to medication and management of related side effects should be made based on the results, ensuring safety while striving to maintain the same dosage.

For grade 1–3 neutropenia, the treatment regimen should not be changed temporarily, and granulocyte colony-stimulating factor (G-CSF) should be added. CBC should be conducted approximately every two days to monitor whether neutrophil counts recover. If there is no recovery, consideration may be given to adjusting the treatment plan. If grade 4 neutropenia persists for≥5 days, despite the addition of G-CSF, Purinostat Mesylate treatment should be permanently discontinued unless the investigator and sponsor agree to continue treatment at a reduced dose in the best interest of the subject.

Patients with multiple myeloma often present with thrombocytopenia and anemia. Close monitoring of platelet counts is essential. For grade 1–3 thrombocytopenia, it is recommended to maintain the dose under supportive treatment with recombinant human thrombopoietin injection (e.g., TPO), recombinant human interleukin-11, or platelet transfusions to prevent life-threatening or severe gastrointestinal or pulmonary bleeding. If bleeding occurs, treatment should be immediately suspended until platelet counts return to baseline levels. If the patient experiences severe anemia (e.g., hemoglobin<60 g/L), red blood cell transfusions or erythropoietin injections may be used to increase red blood cell counts.

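### G-CSF is directed from Grade 1 neutropenia inside the D1–D25 DLT window, so the afebrile neutropenia DLT can be averted and the MTD is in effect G-CSF-supported without being labelled so

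*Protocol*

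**What the plan says.** **Permission.** Section 3.3.1 lists, among supportive drugs allowed from screening through the whole trial, "antihistamines, analgesics, medications to increase white blood cell counts". Section 3.3.2 does not prohibit growth factors.

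**Direction.** Section 8.4, under hematologic toxicity, turns the permission into an instruction. For Grade 1–3 neutropenia, "the treatment regimen should not be changed temporarily, and granulocyte colony-stimulating factor (G-CSF) should be added". It adds that "CBC should be conducted approximately every two days to monitor whether neutrophil counts recover". It also sets a stopping rule that begins "If grade 4 neutropenia persists for≥5 days, despite the addition of G-CSF". No study phase is exempted, and the same text places these reactions early in treatment.

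**DLT and MTD.** Section 3.4 counts as a DLT, within 25 days of the first dose, "Grade 4 neutropenia without fever lasting ≥ 5 days", as well as febrile neutropenia with ANC below 1.0 × 10^9/L. Section 3.5 requires at most 1 DLT among 6 subjects and says "the highest dose that meets this criterion will be defined as the MTD". Neither section mentions G-CSF.

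**Continuation phase.** The Section 3.2.5 table applies only to continuation dosing. At ANC 0.5–0.75 × 10^9/L it says "interrupt treatment until ANC recovers to 1.0 × 10^9^ /L, then continue treatment at the original dose".

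**The concern.** Finding DLTs and the MTD is a primary purpose, and the result is meant to inform the Phase II regimen. The afebrile neutropenia DLT depends on how deep and how long the neutropenia is. G-CSF is given to lessen both. A subject who would have spent five or more days at Grade 4 without support may, when treated from Grade 1 as Section 8.4 directs, never reach Grade 4 or may leave it sooner. No DLT is then recorded and escalation proceeds.

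The recorded result is a true statement about the drug given with G-CSF. The risk is that the dose is later read as tolerable without it, because nothing in Section 3.5 or in the dose-selection text of Section 3.2.3 attaches that condition.

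**Working it through.** **1. Which rule governs neutropenia in D1–D25.** The Section 3.2.5 table is confined to the continuation phase. For the single- and multiple-dose phases, Section 3.2.5 says only what to do once a DLT has occurred. Short of a DLT, Section 8.4 is the only neutropenia-specific management rule, so the G-CSF direction applies in the DLT window.

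**2. How easily it is triggered.** Entry requires ANC of at least 1.5 × 10^9/L (Section 4.4). Appendix 14.3 puts Grade 1 between the lower limit of normal and 1500/mm³, which is the same 1.5 × 10^9/L. A subject can therefore enter in the Grade 1 range, and little or no fall is needed to meet the Section 8.4 trigger.

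**3. Thresholds side by side.** Section 3.4: Grade 4, no fever, at least 5 days, G-CSF not mentioned. Section 8.4: Grade 4, at least 5 days, despite G-CSF. The second is a stopping rule, but it shows that a supported duration was in view there. Sections 3.4 and 3.5 carry no such qualifier.

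**4. The escalation rule.** Seven groups of 3 to 6 subjects give 7 × 3 = 21 and 7 × 6 = 42, matching the planned 21–42. Under the rules in Section 3.2.4, a dose with per-subject DLT probability p is passed on 0/3, or on 1/3 followed by 0/3:

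P(pass) = (1 − p)³ + 3p(1 − p)⁵

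At p = 0.40: 0.216 + 0.093 = 0.309.

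**5. Illustration; both inputs are assumptions.** Let neutropenia be a share s of DLTs and let G-CSF avert a fraction f of those. The observed rate is p = p0 × (1 − s × f). For p0 = 0.40 and s = 0.5, f = 0.25 gives p = 0.350 and P(pass) = 0.275 + 0.122 = 0.397; f = 0.5 gives p = 0.300 and P(pass) = 0.343 + 0.151 = 0.494.

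| True DLT rate p0 | No G-CSF effect | s = 0.25, f = 0.25 to 0.5 | s = 0.5, f = 0.25 to 0.5 |
| --- | --- | --- | --- |
| 0.33 | 0.434 | 0.475 to 0.518 | 0.518 to 0.605 |
| 0.40 | 0.309 | 0.351 to 0.397 | 0.397 to 0.494 |
| 0.50 | 0.172 | 0.209 to 0.252 | 0.252 to 0.351 |

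**6. Sensitivity to the assumed split.** Suppose instead that non-neutropenic DLTs occur independently at 10% and the unsupported total is 40%. The neutropenic part is 1 − 0.60/0.90 = 0.333. If half is averted, the observed rate is 1 − 0.90 × (1 − 0.167) = 0.25 and P(pass) = 0.600. With other-DLT rates of 5%–10% and averted fractions of 25%–75%, P(pass) runs from 0.444 to 0.839, against 0.309. The direction never changes, but the size follows the assumptions.

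**7. The continuation-phase conflict.** ANC 0.5–0.75 × 10^9/L is Grade 3. Section 8.4 leaves the regimen unchanged and adds G-CSF; Section 3.2.5 stops dosing until ANC reaches 1.0. Both cannot be followed. This lies outside D1–D25 and does not affect the MTD.

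**The case against.** **Scoring is not really open.** A reader might infer that Section 3.4 leaves the scoring of supported counts undefined. Read literally, it does not: it counts observed Grade 4 neutropenia by CTCAE 5.0 with no exception for support, and the stopping rule in Section 8.4 points the same way. This stands. The issue is that G-CSF alters the event before it can be scored, and that the resulting MTD is unlabelled.

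**A supported MTD is legitimate.** Nothing in the protocol plans unsupported dosing, and Section 8.4 openly aims to keep subjects on dose. This also stands: the MTD misleads only if later dosing omits G-CSF. The protocol does not say which applies.

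**Other criteria catch serious cases.** Febrile neutropenia, Grade 4 for at least 5 days despite G-CSF, interruption beyond 14 days (outside hematologic toxicity in acute leukemia) and the important-medical-event clause all count. Acute leukemia has its own hematologic clause. Escalation weighs other safety data, and Section 3.2.3 allows the dose below the MTD to go to Phase II. These limit the bias, but the neutropenia criteria do not capture an afebrile Grade 4 episode that G-CSF prevented or cut short.

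**The size has no source.** Correct. Neutropenia is an anticipated event in Section 8.3.1 and bone marrow is a target organ in the chronic toxicity studies. But neutrophils rose in the acute dog study, and the chronic dog study reports falls in platelets and reticulocytes, not neutrophils. Passing one dose is also not the same as declaring a wrong MTD, since up to six evaluable subjects are required at the dose below.

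**The entry count.** A reader might also infer that entry ANC is growth-factor-supported, because inclusion criterion 5 asks for "no transfusion of platelets, red blood cells, or hemoglobin within the 2 weeks prior to screening" and does not mention growth factors. A washout would be a design preference; nothing in the text is contradictory there.

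**Conclusion.** The point holds in a limited form. Following Section 8.4 during D1–D25 can lower the count of afebrile neutropenia DLTs, and the MTD in Section 3.5 is in effect a G-CSF-supported dose that the protocol does not label. The direction, toward a higher MTD, follows from the text together with the purpose of G-CSF. The size does not: every percentage above rests on an assumed neutropenia share and an assumed averted fraction.

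A reader might infer that the MTD will simply be too high. The documents do not support that. It would be too high only for dosing without G-CSF, only if neutropenia contributes materially to DLTs, and subject to the remaining DLT criteria. The Section 8.4 versus Section 3.2.5 conflict at ANC 0.5–0.75 × 10^9/L is a real but separate inconsistency. Both merit an amendment.

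**What to change.** (a) In Sections 3.3.1 and 8.4, for D1–D25, do not give G-CSF prophylactically or for afebrile Grade 1–3 neutropenia unless the investigator documents medical necessity. Allow it for febrile neutropenia and at Grade 4. Keep the blood count about every two days: scheduled counts fall on D15 and then D25, a 10-day gap that cannot resolve a 5-day criterion.

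(b) In Section 3.4, confirm that observed Grade 4 days count whether or not G-CSF is given, and list G-CSF use per subject at each escalation decision.

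(c) If Section 8.4 is kept as it is, state in Section 3.5 that the MTD is with G-CSF support and that the Phase II dose carries the same support.

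(d) Separately, for the continuation phase, amend Section 8.4 to match Section 3.2.5: interrupt at ANC 0.5–0.75 × 10^9/L until it recovers to 1.0.

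**Cost.** These are wording changes with no new procedures; concomitant drugs and their timing already go into the eCRF. Option (a) may produce a few more DLTs or a lower MTD. If a dose is held for neutropenia and not made up, the subject has 3 of 4 doses (75%), below the 80% needed in Section 3.2.4, and without a DLT is not evaluable. The medical-necessity clause keeps G-CSF available to any subject who needs it.
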